## Methods

### Patient Selection

Patients admitted to any of the participating centers with an acute or recent myocardial infarction, who are not treated by direct or rescue angioplasty, and who are stable during the first 48 hours after the acute event, are screened for the study. Patients < 80 years of age are considered suitable for the study when they have definite myocardial infarction, as demonstrated by an significant rise in creatine kinase-MB levels (twice the upper limit of normal: ULN), 1 mm ST segment elevation in two or more standard leads or 2 mm ST segment elevation in two contiguous chest leads, and/or the development of Q waves.

The criteria for exclusion are: viability testing technically not possible (poor echo-window), contraindications for dobutamine echocardiography (arrhythmia), and coronary angiography (severe diabetic nephropathy or known contrast-allergy), serious life-threatening non-cardiac illness, ECG abnormalities making the evaluation of the ST segment impossible (left bundle branch block, pacemaker), and an unreliable follow-up.

The study complies with the Declaration of Helsinki and all ethics committees of the participating centers have approved the protocol. All eligible patients provide written informed consent.

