### Follow-up

Patients will be followed for a period of three years. Follow-up data will be obtained of all patients during visits at the outpatient clinic in the first year, and by telephone interview in the second and third year of follow-up. Left ventricular function (volumes and ejection fraction) is determined by echocardiography at 3 months, 6 months, and 1 year of follow-up.

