### Statistical design

The VIAMI-trial is conducted to investigate the differences in clinical outcome between an invasive and a conservative strategy in patients with demonstrated viability in the infarct-area. The expected event rate in the viability positive group is estimated to be 35 percent. To demonstrate with a power of 80% (α = 0.05, two-sided) that PCI leads to a 50% reduction in event rate in the invasive group compared to the conservative group, 200 patients will be needed in each group. Therefore, we intend to randomize a total of 400 patients in this trial, with interim analysis after 200 included patients.

The formal stopping rules for the study are the following: If one of the treatment strategies appears significant superior at interim analysis (P ≤ 0.01), the study will be stopped.

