### Statistical analysis

Baseline descriptive data will be presented as mean ± standard deviations (SD). Differences in clinical and echocardiographic variables will be assessed by unpaired Student's *t *test. Differences between proportions will be assessed by chi-square analysis; a Fisher's exact test will be used when appropriate. Event-free survival curves are computed with the Kaplan-Meier method, and the differences between these curves are tested with a Mantel-Cox log-rank test. A primary endpoint analysis is planned at 30 days, 6 months, and 1 year of follow-up. Subgroup analyses are planned to determine whether the treatment effect is more or less pronounced in certain subgroups. The data will be subgrouped by sex, age, diabetes, anterior infarction, time from onset of symptoms to treatment, and the use of thrombolytics. All analyses will be performed on an intention-to-treat basis. Also, the outcome per-protocol will be evaluated. Such an analysis seems worthwhile, as it will reflect the true influence of PCI on post-thrombolytic ischemic events.

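### Effect modification by age is to be examined only through age subgroups, which loses information if the treatment effect changes roughly linearly with age

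*Protocol article*

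**What the plan says.** The Statistical analysis section gives the aim of these analyses: "Subgroup analyses are planned to determine whether the treatment effect is more or less pronounced in certain subgroups". The method follows in the next sentence: "The data will be subgrouped by sex, age, diabetes, anterior infarction, time from onset of symptoms to treatment, and the use of thrombolytics". Age therefore gets the same treatment as sex and diabetes. The methods named in that section (t test, chi-square or Fisher's exact test, Kaplan-Meier curves with a log-rank test) all compare groups, and none takes age as a continuous modifier. The article gives neither the number of age groups nor a cut-point.

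On age itself, Patient Selection sets only an upper limit: "Patients < 80 years of age are considered suitable for the study". It states no lower limit, mean or spread.

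**The concern.** Age is recorded in years for every patient. Grouping treats everyone on one side of a boundary as alike and drops any trend within groups. If benefit rises or falls steadily with age, part of the evidence is discarded.

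There is little to spare. The stated rates and sample size imply about 105 primary events, and an interaction is estimated far less precisely than a main effect. What is at stake is the chance of detecting a real age gradient in a secondary analysis. The comparison of the two strategies does not depend on it.

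**Working it through.** **Inputs from the article.** Statistical design gives the event rate ("The expected event rate in the viability positive group is estimated to be 35 percent"), the halving and error rates ("To demonstrate with a power of 80% (α = 0.05, two-sided) that PCI leads to a 50% reduction in event rate") and the size ("200 patients will be needed in each group"). Follow-up gives three years.

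**Assumed, because the article does not say.** The 35% is a three-year risk in the conservative arm. The log hazard ratio is linear in age. Age follows one of three shapes: normal; normal with mean 62 and SD 11, truncated at 30 and 80; or uniform.

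**1. The plan's own figures.** It gives none for the age analysis. Its one related figure, 200 per group, is not reproduced: 35% v 17.5% at 80% power and two-sided 0.05 needs 99 per group (110 with continuity correction), and 200 gives 98% power. That is a separate matter. Only the planned numbers and rates are used here:

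200 × 0.35 + 200 × 0.175 = 70 + 35 = 105 events.

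**2. Information kept by grouping.** For a linear interaction,

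fraction kept = between-group variance of age / total variance of age.

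For a median split of normal age the group means lie at ±0.798 SD, so the fraction is 0.798² = 0.637 = 2/π and the loss is 36.3%.

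Standard errors give the same answer:
- Continuous age, per SD: √(1/70 + 1/35) = 0.207.
- Median split, with about 35 and 17.5 events per half: √(2/35 + 2/17.5) = 0.414, for groups whose mean ages differ by 1.596 SD.
- Ratio of z values: (1.596/0.414) / (1/0.207) = 0.798; squared, 0.637.

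Loss for other groupings:

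| Grouping | Normal | Truncated at 80 | Uniform |
|---|---|---|---|
| Four equal groups | 13.9% | 11.5% | 6.2% |
| Three equal groups | 20.7% | 18.0% | 11.1% |
| Cut at median | 36.3% | 33.7% | 25.0% |
| Cut at 40th percentile | 37.8% | 33.8% | 28.0% |
| Cut at 30th percentile | 42.4% | 37.7% | 37.0% |
| Cut at 25th percentile | 46.1% | 41.3% | 43.8% |
| Cut at 20th percentile | 51.0% | 46.3% | 52.0% |

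For the two symmetric shapes, cuts at the mirror-image upper percentiles lose the same. For the truncated shape a high cut loses somewhat more. The first two rows assume a one-degree-of-freedom trend across ordered groups; an unordered heterogeneity test would do worse against a linear gradient.

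**3. Power, by hand.** Let the hazard ratio change 2.5-fold from 1 SD below to 1 SD above mean age. The interaction is ln(2.5)/2 = 0.458 per SD, and z = 0.458/0.207 = 2.21.
- Continuous: Φ(2.21 − 1.96) = 60%.
- Three groups: 2.21 × √0.793 = 1.97, power 50%.
- Median split: 2.21 × 0.798 = 1.77, power 42%.

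**4. Power, by simulation.** Two separately coded Cox simulations (1500 and 1000 trials per scenario) used 200 per arm, truncated age as above, main hazard ratio ln(0.825)/ln(0.65) = 0.447, a prognostic age effect of 0.2 per SD, censoring at three years and a 0.05 test. A range shows the two runs; single values come from one run.

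| Change in hazard ratio, −1 SD to +1 SD | Continuous | Three ordered groups | Median split | Cut at 70 |
|---|---|---|---|---|
| 2-fold | 37-40% | 30% | 25-26% | 23% |
| 2.5-fold | 56-58% | 47% | 39-41% | 36% |
| 3-fold | 73% | 63% | 51-53% | 47% |

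With no gradient, one run rejected in 4-5% of trials for continuous age, median split and cut at 70. The other gave 6.5% (continuous), 5.6% (three groups) and 5.0% (median split). That slight excess for continuous age is far too small to explain a 17-point difference in power.

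**5. The reverse case.** If the effect is a step at the median of normal age, the correlation between age and the step is again 0.798. A linear term then keeps only 0.637 of the information and the median split keeps all of it.

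**The case against.** **The size is not fixed by the plan.** A reader might infer that this plan throws away a third of the information on age. The article does not support that. The figure needs two groups, a cut near the median, roughly normal age and a linear gradient, and none of these is stated. This objection stands, so the loss is given here only as a conditional range.

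**Detail is left to fuller documents.** Cut-points and the form of a modifier are commonly set in the full protocol or analysis plan, and a supplementary continuous analysis is not ruled out. This stands as far as the missing cut-points go; they are no part of the point. It does not remove the point, because grouping is the method the article states.

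**The purpose concerns subgroups.** The stated aim asks about certain subgroups, so it cannot be read as strictly asking about a gradient. That is fair. Contrasts between groups remain a legitimate display.

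**The advantage depends on the shape.** Continuous age does better if the gradient is roughly linear and worse if the effect is a step at the cut. Nothing in the article settles which. This stands, and it is why the fix includes a non-linearity check.

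**The inputs are assumed and the gain is limited.** The age distribution, prognostic effect and gradients are not in the article, and no time horizon is attached to the 35%. If it is a three-year risk, the endpoint analyses at 30 days, 6 months and 1 year would have fewer events. Even with continuous age, power for a 2-fold gradient is only about 40%. All of this stands.

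**Time from onset.** A reader might extend the point to time from symptom onset to treatment. That would first require redefining the variable so that it has the same meaning in both arms, and no calculation here covers it. It is not claimed.

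**Conclusion.** The point holds as a minor one. The article states grouping as its method for a continuous candidate modifier, and under a roughly linear gradient every grouping examined loses information: about 34-36% for a median split of roughly normal age (25% if age is uniform), about 6-21% for three or four equal ordered groups, and about 41-52% for a single cut at the 20th or 25th percentile. At the assumed 2.5-fold gradient, a median split costs about 17 percentage points of interaction power and three ordered groups about 9 (56% to 47% within one run).

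The existence of a loss rests on approximate linearity. Its size rests also on the unstated grouping and the assumed age distribution, and the power figures on the assumed event count and gradient. It does not follow that the primary comparison, the sample size or the follow-up is affected.

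**What to change.** Add to the Statistical analysis section: *Effect modification by age will be tested as a treatment-by-age interaction with age continuous, in a Cox model by intention to treat. Departure from linearity will be checked with a quadratic or spline term. The hazard ratio will be shown across age, and age subgroups will be presented for display.* The handling of sex, diabetes, anterior infarction and thrombolytics can stay as it is.

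The cost is one sentence and one extra model, with no new data, visits or patients. The downside is that the default test assumes a roughly linear gradient and is less efficient than grouping if the effect is a step at the cut. The non-linearity check and the displayed subgroups limit that risk but do not remove it.

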### Current status

Enrollment of patients started April 1, 2001. Recently, an interim analysis was performed after the inclusion of 200 patients, having a 30 day follow-up. The Clinical Event Committee recommended continuation of the trial.

## Conclusion

The VIAMI-trial is the first multicenter, randomized, controlled clinical trial, investigating the clinical benefits of percutaneous catheter intervention of the infarct-related artery in patients with demonstrated viability in the early, subacute phase of myocardial infarction.
